##### Estimation of Work Rate in Watts

The work rate (watts) will be obtained by using the individual’s body mass and the $\dot{V}O_{2}$ (mL kg^−1^ min^−1^), as described in Equation 3 [55].

(3)
$$\begin{array}{rl} \text{Work rate [W]} & =\frac{\text{Body mass}\times \left(\dot{V}O_{2\text{CWR}}-7\right)}{1.8}\times 0.164 \end{array}$$

where the individual’s body mass will be expressed in kilograms (kg) and the $\dot{V}O_{2}$ (mL kg^−1^ min^−1^) is the target $\dot{V}O_{2CWR}$ obtained in step 3 (Equation 2). The result of Equation 3 will determine the CWR (Watts) performed during the ICU-CARE CPET protocol on the cycle ergometer.

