Typically, evaluation of $\dot{V}O_{2peak}$ and $\dot{V}O_{2}$ on/off kinetics requires multiple exercise sessions in order to first determine participant-specific $\dot{V}O_{2peak}$ and then to use these values to derive a constant work rate (CWR) as a percentage of $\dot{V}O_{2peak}$ or ventilatory thresholds [27-30]. However, this approach can limit recruitment and compliance, and is especially problematic for clinical research with vulnerable or disadvantaged participant groups [31]. Moreover, caregivers of ICU survivors are known to experience depressive symptoms for at least 1 year following discharge [32], which may also impact participation due to the inability or unwillingness to arrange and/or accompany to multiple sessions. Crucially, designing an efficient and simple protocol is critical for both the survivor and caregiver to foster recruitment and compliance. When $\dot{V}O_{2peak}$ and $\dot{V}O_{2}$ on/off kinetics are evaluated in a single session, as has been done by previous researchers [7,14,33], a uniform CWR is often prescribed regardless of fitness level and many times based on subjective parameters, which prevents accurate data comparison between participants. Furthermore, the timing of the phases of the exercise (ie, CWR, ramp, and recovery) within a single session protocol requires standardization, considering relatively short CWR or the implementation of an active recovery, which may compromise data quality for evaluating on/off kinetics [7,28].

Our team has recently developed a single-session CPET protocol for a combined assessment of $\dot{V}O_{2peak}$ and $\dot{V}O_{2}$ on/off kinetics in healthy young adults [28]. In this study, we showed that CWR intensity can be estimated a priori [16] from a Hansen-Wasserman population-based formulae of $\dot{V}O_{2peak}$ (mL kg^−1^ min^−1^), recommended by the American Thoracic Society (ATS) and the American College of Chest Physicians (ACCP) committee [17], relative to sex, body mass, measured $\dot{V}O_{2rest}$ (mL kg^−1^ min^−1^), multiplied by a desired intensity of 30 % $\dot{V}O_{2reserve}$. The estimated $\dot{V}O_{2peak}$ was in good agreement compared to real values measured later in the CPET, where participants achieved steady state (SS $\dot{V}O_{2}$) and adequate return to baseline during the CWR and recovery phases of the protocol.

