#### Constant Work Rate Phase (On-Kinetics)

The CWR phase will entail a 5-minute steady-state moderate-intensity upright cycling exercise at the desired intensity of 30%, relative to the individual’s estimated $\dot{V}O_{2reserve}$ (as described below in the .$\overset{˙}{\;V}O_{2reserve}$Calculation section) to perform exercise, with a cadence of 60 rpm [28]. In a recent publication, our team used a 4-step process to standardize and determine the optimal CWR exercise intensity during a CPET protocol [28]. We will adopt and adapt these steps to derive a CWR intensity for ICU survivors, as outlined below.

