##### ICU Survivor Prediction Equation for$\dot{V}O_{2peak}$

In this first step, to determine CWR, a recent Canadian adult (≥40 years of age) normative (50th percentile) and sex-specific equation (Equation 1) [54] will be used to predict $\dot{V}O_{2peak}$. Subsequently, an ICU correction factor of 0.75 (ICU0.75) is to be multiplied based on an average of 25% $\dot{V}O_{2peak}$ reduction in ICU survivors, previously described in the literature [5,7,21].

(1)
$$\begin{array}{rl} \text{Estimated }\dot{V}O_{2\text{peak}} & =(\left(0.012905699\cdot H)+(0.007291081\cdot BM\right)\\ \;+(0.564188602\cdot S)-(0.016521850\cdot A)\\ \;-0.076072067)\times ICU0.75 \end{array}$$

where age in years, BM = body mass (kg), H = height (cm), S = sex: male = 1, female = 0, and ICU0.75 = ICU correction factor of 0.75.

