### Data Analysis

Similar to the $\dot{V}O_{2}$ analysis conducted on healthy adult populations [28], $\dot{V}O_{2}$ on-kinetics (rest-to-exercise transition), $\dot{V}O_{2peak}$, and $\dot{V}O_{2}$ off-kinetics (exercise-to-recovery transition) will be analyzed in the ICU-CARE CPET within a single bout—reporting the measured and predicted $\dot{V}O_{2peak}$ (mL kg^−1^ min^−1^), measured SS $\dot{V}O_{2}$ at CWR (mL kg^−1^ min^−1^), “actual” calculated 30% $\dot{V}O_{2reserve}$ (mL kg^−1^ min^−1^), and targeted intensity achieved at CWR as a percentage (%). Additionally, NIRS will be analyzed to evaluate skeletal muscle microvascular oxygenation. The primary variables will be pulmonary $\dot{V}O_{2}$, deoxyhemoglobin (HHb; deoxy[Hb+ Mb]), and TSI ($\frac{\left[oxy\left(Hb+Mb\right)\right]}{\left[oxy\left(Hb+Mb\right)\right]+\left[deoxy\left(Hb+Mb\right)\right]}*100$), measured noninvasively at a sample rate of 10 Hz.

Skeletal muscle oxygenation measured by NIRS (Portamon, Artinis Medical Systems) will be transmitted wirelessly into OxySoft software, time-synched with the metabolic cart with real-time impulse by inserting key commands on the NIRS computer (listed in Figure 1). On OxySoft, export NIRS data to Microsoft Excel, then adjust to timestamps as described above and illustrated in Figure 2. For a combined analysis, $\dot{V}O_{2}$ and NIRS data will be preprocessed using a customized LabVIEW code (LabView v20.0.01, National Instruments Corp), specifically designed to perform the required analyses. The first analysis removes noise and motion artifacts. Initially, outliers will be removed by applying 2 standard deviations in a window size of 7 seconds, then applying a 350-second moving average, linearly interpolated to provide second-by-second values [52]. Then, the data is resampled at 1 Hz and time-aligned with each transition to be synchronized with the metabolic cart.

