## Results

### Outcome Measures

Our primary methodological outcome for this study will be the feasibility of recruitment and completion of the protocol. The secondary outcome will be validation of a priori physiological equations through assessment of agreement between predicted and measured variables of $\dot{V}O_{2peak}$ and $\dot{V}O_{2CWR}$. Physiological observations of exercise capacity and skeletal muscle oxygenation derived from the protocol will also be considered secondary outcomes.

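### Equation 3 gives 0 W or less for many older or heavier eligible women (very few men), so their constant-work-rate load cannot be set at 30% of VO2reserve

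*Protocol article*

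**What the plan says.** All references are to the protocol article.

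- Constant Work Rate Phase: every participant is to do a "5-minute steady-state moderate-intensity upright cycling exercise at the desired intensity of 30" percent of estimated VO2reserve.
- ICU Survivor Prediction Equation (Equation 1): VO2peak is predicted from height, mass, sex and age, and then "an ICU correction factor of 0.75 (ICU0.75) is to be multiplied".
- VO2reserve Calculation and Equation 2: rest is fixed at 3.5 mL/kg/min, and the target VO2CWR is rest plus 30% of the reserve.
- Estimation of Work Rate in Watts (Equation 3): the target is converted to a load, and "The result of Equation 3 will determine the CWR (Watts) performed during the ICU-CARE CPET protocol on the cycle ergometer". No step covers a result of zero or below.
- Outcome Measures: "The secondary outcome will be validation of a priori physiological equations through assessment of agreement between predicted and measured variables of" VO2peak and VO2CWR.
- Data Analysis: the report will include the "targeted intensity achieved at CWR as a percentage".
- Inclusion and Exclusion Criteria: both sexes are eligible from 18 years with no stated upper age limit; a BMI of 40 or more is excluded.

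**The concern.** An ergometer cannot deliver a negative load. If the chain returns one for eligible participants, the operator must improvise, and by the protocol's own equations no load meets the 30% target. Three things are at stake.

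- **Standardized relative intensity.** The failure would follow sex, age and body mass, while results are to be reported separately by sex.
- **Uniform loads.** Everyone at the floor would get one load whatever their predicted fitness. The Introduction objects to earlier single-session work because "a uniform CWR is often prescribed regardless of fitness level".
- **VO2CWR agreement.** In floored participants a predicted value below 7 mL/kg/min would be paired with a load that Equation 3 equates to 7. By that equation, disagreement is expected before any data are collected.

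**Working it through.** **Inputs.** All constants come from Equations 1 to 3, with the coding "BM = body mass (kg), H = height (cm), S = sex: male = 1, female = 0" and age in years. One assumption is needed: the unit of Equation 1 is not stated. Its coefficients give values of about 1 to 3, so I read it as L/min and multiply by 1000/mass, because Equation 2 needs mL/kg/min. The article gives no worked wattage to reproduce.

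**Step 1, threshold.** Let P be the corrected predicted VO2peak.

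- Equation 3: W = mass × (VO2CWR - 7) / 1.8 × 0.164, so W > 0 only if VO2CWR > 7.
- Equation 2: VO2CWR = 3.5 + 0.3 × (P - 3.5).
- VO2CWR = 7 gives P = 3.5 + 3.5/0.3 = 15.17 mL/kg/min, or 15.17/0.75 = 20.22 before the ICU factor.

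**Step 2, one case in full.** Woman, 65 y, 163 cm, 80 kg:

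- Equation 1 before the factor: 2.1036 + 0.5833 + 0 - 1.0739 - 0.0761 = 1.5369 L/min.
- P = 1.5369 × 0.75 × 1000/80 = 14.41.
- VO2CWR = 3.5 + 0.3 × 10.91 = 6.77.
- W = 80 × (6.77 - 7) / 1.8 × 0.164 = -1.7 W (unrounded inputs).
- Without the 0.75 factor: P = 19.21, VO2CWR = 8.21, W = +8.8 W.

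**Step 3, further cases.** Intensity at 0 W is (7 - 3.5)/(P - 3.5).

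| Participant | P | Target VO2CWR | W | 0 W as % of estimated reserve |
|---|---|---|---|---|
| Woman 65 y, 163 cm, 80 kg | 14.41 | 6.77 | -1.7 | 32.1 |
| Woman 70 y, 163 cm, 70 kg | 14.80 | 6.89 | -0.7 | 31.0 |
| Woman 75 y, 160 cm, 95 kg | 11.39 | 5.87 | -9.8 | 44.4 |
| Man 60 y, 176 cm, 85 kg | 21.07 | 8.77 | +13.7 | not affected |

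**Step 4, where the chain fails.** Solving P = 15.17 for mass gives the BMI from which the load is 0 W or less:

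| Age | Woman, 163 cm | Man, 176 cm |
|---|---|---|
| 50 | 35.0 | outside eligible range |
| 60 | 30.2 | outside eligible range |
| 65 | 27.8 | outside eligible range |
| 70 | 25.4 | 40.0 (excluded) |
| 75 | 23.0 | 38.0 |
| 80 | not tabulated | 35.9 |

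For women, heights of 155-172 cm move these thresholds by less than 1 BMI unit.

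**Step 5, how many (assumed mixes).** Virtual cohorts were run with mean age 50-65 (SD 14), mean BMI 26-30 (SD 5.5, below 40), 30-50% women, and heights of 163 (SD 6.5) cm for women and 176 (SD 7) cm for men. Results at 0 W or less:

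- women 15.7-58.0%;
- men 0.15-3.3%;
- overall 4.8-30.6%, that is 0.048 × 48 = 2.3 to 0.306 × 48 = 14.7 participants.

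The youngest, leanest mix gives 5-8% overall. Among those affected, 0 W implies a median of 33-35% of estimated reserve (90th percentile 40-45%). The gap between 7 and the target has a median of 0.3-0.5 mL/kg/min (90th percentile 0.8-1.2).

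**The case against.** The strongest reply accepts the algebra and disputes the consequence.

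- **Small miss.** For the 65-year-old woman above, unloaded pedalling is 32.1% of estimated reserve rather than 30%, and that reserve is itself approximate. The 30% target exists to stay below the ventilatory threshold, reach steady state and spare the ramp; nothing here shows that 0 W defeats those aims. This stands for most affected participants, but not for the tail at 40-45%.
- **Unknown frequency.** The range is about sixfold, and the stair-climbing, oxygen and heart-disease exclusions were not modelled. They may push it towards the low end. Weight alone rarely triggers the failure before about 50: at 163 cm the threshold BMI is 39.8 at 40 y and 37.4 at 45 y. This stands, and prevalence should be read as conditional. The direction does not depend on it.
- **Visible anyway.** Achieved intensity will be reported, and testing the equations is a stated outcome. True, but reporting afterwards does not set a load. Actual VO2 at 0 W is also unknown in these patients, so the gap is built in only by Equation 3's own intercept.
- **Shared loads.** Those at the floor share a load because all have low predicted fitness, so the parallel with a uniform CWR is partial. Fair; it applies only within that group.
- **Operational detail.** A condensed article may leave a minimum load to the full protocol. However, the article prints the whole chain and says its result fixes the load. A floor rule elsewhere would still leave the 30% statement untrue for these participants.

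**Conclusion.** The concern holds. For eligible women below the 15.17 mL/kg/min threshold, the printed rule returns a load that cannot be set, and no achievable load meets the stated target. The 0.75 factor, the 30% target and the 7 mL/kg/min intercept produce this together. The pilot described under Anticipated Feasibility used other population equations, and Equation 1 was adopted after it, so the article reports no trial of this chain in ICU survivors.

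The threshold and worked cases rest only on the printed equations and the L/min reading. The shares affected rest on assumed age, sex and body-size mixes. The effect is confined to CWR intensity, VO2CWR agreement and the interpretation of on-kinetics. The primary feasibility outcome, VO2peak, its agreement analysis and the sample size do not use Equation 3. This should be fixed before testing starts, but it does not threaten the study.

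**What to change.** 1. Before the first participant is tested, run Equations 1 to 3 over the eligible range of sex, age, height and mass.
2. Add one rule to Estimation of Work Rate in Watts. For example: if Equation 3 gives a value at or below the ergometer minimum, use unloaded pedalling or the lowest setting, the same for all such participants. Flag them.
3. Keep the Equation 2 target in the main VO2CWR agreement analysis, so that a failure of the a priori chain stays visible.
4. Add a sensitivity analysis of VO2CWR agreement and on-kinetics. It should either exclude flagged participants or use the VO2 implied by the load applied, 1.8 × W / (0.164 × mass) + 7.
5. Limit the 30% statement to participants for whom the formula gives an achievable load.

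The cost is a one-off calculation, a short amendment, one flag variable and one sensitivity analysis, with no extra patients or visits. The drawback is that flagged participants are tested somewhat above 30% of estimated reserve, which the report must say. Acting early matters because loads chosen ad hoc cannot be standardized afterwards.

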### Incremental Phase

The incremental phase of the protocol will be based on the information obtained from the self-reported staircase question [56] and modified Medical Research Council (mMRC) dyspnea scale [57] during the recruitment process. For the staircase question, participants will be asked, “How many floors can you walk up quickly without stopping?,” during the recruitment process. Based on their responses, the increments will be defined as follows: one floor (5 W min^−1^; 50 W), two floors (10 W min^−1^; 100 W), three floors (15 W min^−1^; 125‐150 W), and four floors (20 W min^−1^; 200 W). For the mMRC dyspnea scale, participants’ severity of breathlessness will be reported based on activity descriptors and mMRC grade between 0 and 4 with their respective Watt equivalent, as described in Table 1. Participants will cycle until the termination criteria are met, as described above.

**Table 1. T1:** Modified Medical Research Council (mMRC) dyspnea scale.

Grade	Activity descriptor	Ramp
0	Strenuous activity, not troubled by breathlessness (eg, cycling and shoveling heavy snow)	20 W min^−1^
1	Walking up an incline causes shortness of breath	15 W min^−1^
2	Walking two blocks and experiencing breathlessness	10 W min^−1^
3	Walking short distances and needs to catch breath (eg, 100 ft, or room to room)	10 W min^−1^ for males, 5 W min^−1^ for females
4	Cannot get dressed or shower without shortness of breath	No CPET^a^

a CPET: cardiopulmonary exercise test.

### Recovery Phase (Off-Kinetics)

After the cessation of exercise, participants will stop pedaling, remain seated on the cycle ergometer, and start passive recovery for 10 minutes. $\dot{V}O_{2}$, deoxyhemoglobin (HHb), and tissue saturation index (TSI) responses will be used to evaluate off-kinetics.

Figure 2 displays the ICU-CARE CPET protocol including (1) resting phase: 3 minutes baseline $\dot{V}O_{2}$ measurements, no pedaling, seated on the bike; (2) constant work rate phase (CWR): 5 minutes pedaling at 30%$\overset{˙}{\;V}O_{2reserve}\;\left(\overset{˙}{V}O_{2peak\;predicted}-\overset{˙}{V}O_{2rest}\right)$, whereby $\dot{V}O_{2peakpredicted}$ is estimated a priori using population-based estimates and an ICU $\dot{V}O_{2peak}$ multiplied by a correction factor of 0.75; (3) incremental phase: $\dot{V}O_{2peak}$ is assessed through a ramped cycling exercise, based on self-reported functional status (5, 10, 15, or 20 W min^−1^), until termination criteria are met (as described in the Safety and Termination Criteria section above); and (4) recovery: 10-minute, no pedaling.

### Data Analysis

Similar to the $\dot{V}O_{2}$ analysis conducted on healthy adult populations [28], $\dot{V}O_{2}$ on-kinetics (rest-to-exercise transition), $\dot{V}O_{2peak}$, and $\dot{V}O_{2}$ off-kinetics (exercise-to-recovery transition) will be analyzed in the ICU-CARE CPET within a single bout—reporting the measured and predicted $\dot{V}O_{2peak}$ (mL kg^−1^ min^−1^), measured SS $\dot{V}O_{2}$ at CWR (mL kg^−1^ min^−1^), “actual” calculated 30% $\dot{V}O_{2reserve}$ (mL kg^−1^ min^−1^), and targeted intensity achieved at CWR as a percentage (%). Additionally, NIRS will be analyzed to evaluate skeletal muscle microvascular oxygenation. The primary variables will be pulmonary $\dot{V}O_{2}$, deoxyhemoglobin (HHb; deoxy[Hb+ Mb]), and TSI ($\frac{\left[oxy\left(Hb+Mb\right)\right]}{\left[oxy\left(Hb+Mb\right)\right]+\left[deoxy\left(Hb+Mb\right)\right]}*100$), measured noninvasively at a sample rate of 10 Hz.

Skeletal muscle oxygenation measured by NIRS (Portamon, Artinis Medical Systems) will be transmitted wirelessly into OxySoft software, time-synched with the metabolic cart with real-time impulse by inserting key commands on the NIRS computer (listed in Figure 1). On OxySoft, export NIRS data to Microsoft Excel, then adjust to timestamps as described above and illustrated in Figure 2. For a combined analysis, $\dot{V}O_{2}$ and NIRS data will be preprocessed using a customized LabVIEW code (LabView v20.0.01, National Instruments Corp), specifically designed to perform the required analyses. The first analysis removes noise and motion artifacts. Initially, outliers will be removed by applying 2 standard deviations in a window size of 7 seconds, then applying a 350-second moving average, linearly interpolated to provide second-by-second values [52]. Then, the data is resampled at 1 Hz and time-aligned with each transition to be synchronized with the metabolic cart.

With exercise starting at zero, subsequent analysis will be performed using a mono-exponential model to fit the pulmonary or primary component of the $\dot{V}O_{2}$ response (ie, phase II) by skipping the cardiogenic phase (ie, phase I), as previously recommended [33,58], left-shifting at 20 s in length [52]. Then, the steady-state $\dot{V}O_{2}$ (SS $\dot{V}O_{2}$ or phase III) will be calculated as the average of the last 2 minutes of the CWR exercise phase [28]. The mono-exponential fitting is characterized by $\dot{V}O_{2}$ parameters, including tau (τ), time delay (TD), amplitude A_0_ and A_1_, and mean response time (MRT), where τ is defined as the time constant of the exponential function, representing the time taken to reach 63% of the steady-state or final value; TD records the delay to the exponential response start (ie, phase II) (the model is not constrained to pass through the origin) before oxygen uptake responds to exercise; A_0_ represents the baseline value (resting $\dot{V}O_{2}$), whereas A_1_ represents the change of amplitude from baseline to steady-state $\dot{V}O_{2}$ (ie, SS $\dot{V}O_{2}$ – baseline value); and MRT, defined as TD + τ, representing the overall time to adjust the rate of $\dot{V}O_{2}$ to changes in workload [28]. At the end of the incremental phase, $\dot{V}O_{2peak}$ will be defined as the highest value of the last 30 seconds before volitional exhaustion after applying a 20-second moving average [59,60]. The quality of the fitting will follow our previous protocol [28]. The analysis of residuals, the degree of linear correlation between the experimental data and fitted function (*r*), the 95% CI band, and the significance level (*P* value) of the estimated parameters are used to determine the quality of the fitting.

The HHb signal will be normalized using a 60-second average before the exercise begins, then analyzed by detecting the nadir, occurring after a sudden decrease in HHb signal, to exclude data not associated with muscular $\dot{V}O_{2}$ dynamics, referring to the muscle pump [61]. After the nadir, HHb increases monoexponentially, representing the $\dot{V}O_{2}$ dynamics during the onset of exercise [27,62-64].

The HHb monoexponential function is expressed in the equation below:

$$HHb\;{\left(t\right)}^{\;}=HHb_{bl}+a\left[1-e^{-\left(t-TD\right)/\tau }\right]$$

where HHb_bl_=HHb baseline, *a*=amplitude, *e*=mathematical constant, *t*=time, TD=time delay, and τ=time constant.

MRT of the HHb is also estimated by the sum of τ and TD, to determine the MRT time constant.

Changes in TSI will be assessed by calculating the difference between baseline (average 30 seconds before CWR) and end of exercise (30-second average before start of recovery) to quantitatively evaluate tissue saturation fluctuation of oxygen uptake within the skeletal muscle, reported as ΔTSI [%] in the equation below:

$$\Delta TSI\;\left[\%\right]={TSI}_{peak}-{TSI}_{bl}$$

where TSI_peak_=30-second average before $\dot{V}O_{2peak}$; TSI_bl_=TSI baseline, 30-second average before commencing exercise.

Secondary variables from the CPET will be collected in an exploratory manner. These include carbon dioxide output ($\dot{V}{CO}_{2})$, respiratory exchange ratio, oxyhemoglobin, heart rate response, peak oxygen pulse, tidal volume, breathing frequency, minute ventilation (VE), ventilatory efficiency (VE/VCO_2_), and breathing reserve. Measured adipose tissue thickness of ≥12.5 mm will define a subgroup of patients with less reliable skeletal muscle NIRS measurements [37]; sensitivity analysis will be undertaken with both inclusion and exclusion of this subgroup in cohort outcomes. Other variables to consider include the CPET time of completion, patient-reported outcomes, and any other additional comments regarding the ICU-CARE CPET protocol experience.

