#### Rest Phase

The rest phase consists of 3 minutes baseline, seated on the upright cycle ergometer without pedaling to establish baseline values for $\dot{V}O_{2}$ and NIRS signals prior to initiating the CWR phase.

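### The stated 350-second moving average is longer than the rest and constant-work-rate phases, so the on-kinetics cannot be recovered and the off-kinetics are distorted; the intended window must be stated

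*Protocol article*

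**What the plan says.** All places are in the protocol article.

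- **Data Analysis, preprocessing.** VO2 and "NIRS data will be preprocessed using a customized LabVIEW code". First, "outliers will be removed by applying 2 standard deviations in a window size of 7 seconds"; the next step is "then applying a 350-second moving average, linearly interpolated to provide second-by-second values". The data are then resampled at 1 Hz and aligned to each transition. The mono-exponential fit (tau, TD, amplitudes, MRT) is described as the analysis that follows. A citation is the only support for the 350-s value.
- **Phase lengths.** Rest Phase: "The rest phase consists of 3 minutes baseline, seated on the upright cycle ergometer without pedaling". Constant Work Rate Phase: "The CWR phase will entail a 5-minute steady-state moderate-intensity upright cycling exercise". Recovery Phase: participants "start passive recovery for 10 minutes".
- **Later steps in Data Analysis.** A 20-s left shift removes phase I. VO2peak is "the highest value of the last 30 seconds before volitional exhaustion after applying a 20-second moving average". HHb is normalised to a 60-s baseline and its nadir is then detected. The TSI baseline is the "average 30 seconds before CWR", and the TSI peak is also a 30-s average.

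**The concern.** A moving average cannot preserve a transient much shorter than its own window. Here the window is longer than the whole phase in which the on-transient is recorded. Applied as written, it would replace the exponential rise with a slow, nearly straight climb, and the fitted tau, TD, amplitude and MRT would describe the filter more than the participant. The brief HHb dip that the plan needs to locate would be averaged away, and the two 30-s TSI values would each be blended with neighbouring phases.

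Kinetics and muscle oxygenation are part of the stated objective and of the second hypothesis, and Data Analysis calls VO2, HHb and TSI its primary variables. The article also offers the method as a standard. A second site that followed the text literally would lose the on-kinetics.

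**Working it through.** **Inputs from the document.** Window 350 s; rest 3 × 60 = 180 s; CWR 5 × 60 = 300 s; recovery 10 × 60 = 600 s; NIRS sampling 10 Hz; fit from 20 s after onset; steady state = mean of the last 120 s of CWR.

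**Inputs assumed (not in the document).** Set A: baseline 3.5, CWR amplitude 6 and peak 16 mL/kg/min, TD 15 s, ramp of 480 or 600 s. Set B: rest 0.28 and amplitude 0.30 L/min, TD 20 s, 10 W/min ramp. True tau is 30, 45 or 60 s in both, there is no noise, and baseline is extended backwards where a window outruns the record.

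**Step 1: window against phases.** 350/300 = 1.17 and 350/180 = 1.94. The window is shorter than recovery (350 < 600).

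**Step 2: what each smoothed CWR point contains.**
- Centred (175 s each side): points at 0–125 s mix rest and CWR; 125–175 s mix rest, CWR and ramp; 175–300 s mix CWR and ramp.
- Trailing: every point mixes rest and CWR, none includes ramp. The window is not even full until 350 − 180 = 170 s into CWR.

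Either way, no CWR point is free of another phase.

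**Step 3: limits that need no simulation.** An instantaneous step smoothed over 350 s rises from 10% to 90% in 0.8 × 350 = 280 s, nearly the whole CWR phase. With a trailing window, the response at time t is close to amplitude × (t − TD − tau)/350, a straight line with no time constant. Its mean over 180–300 s (mid-point 240 s), for tau 45 s in Set A, is 3.5 + 6 × (240 − 15 − 45)/350 = 6.59. The unsmoothed value is 9.45.

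**Step 4: refitting after smoothing.** Each profile was smoothed at 1 Hz, then the mono-exponential was refitted from 20 s after CWR onset and over the 600-s recovery.

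| True tau (s) | On-tau, 350 s centred, Set A | Set B | On-tau, 350 s trailing | Off-tau, 350 s centred, Set A | Off-tau, 350 s trailing, Set A |
|---|---|---|---|---|---|
| 30 | 310–352 | 550–940 | not identifiable | 112–113 | 386–407 |
| 45 | 418–493 | 700–1300 | not identifiable | 125–126 | 487–525 |
| 60 | 565–707 | 910–1970 | not identifiable | 140–141 | 642–714 |

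Not identifiable means that the fit ran to its 5000-s upper bound. The ranges in Set A come from the two ramp lengths. Those in Set B come from whether the ramp response is lagged by TD and tau (lower value) or by tau alone (higher value). The document fixes none of these inputs.

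Steady-state VO2 stays close to its true value with a centred window (9.45 becomes 9.37–9.43 at tau 45 s), but falls to about 6.1–6.8 with a trailing one across true tau of 30–80 s. The trailing form would therefore also spoil the comparison of predicted with measured VO2 at CWR.

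**Step 5: shorter windows for contrast.** A 5-s centred window moves on-tau by about 0.1 s. If 350 meant samples, 350/10 Hz = 35 s. Centred, 35 s adds about 1 to 3 s to tau. Trailing, it adds about 9 to 14 s depending on the input set (for example 45 becomes 54.3 s in Set A, with TD moving from 15 to 26.2 s).

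**The case against.** The strongest reply is that this is a slip, not a choice. The neighbouring windows are 7, 20, 30 and 60 s, and 350 samples at 10 Hz would be 35 s. Smoothing happens after acquisition, so the raw data survive and can be reprocessed. Both points stand. They do not settle the matter, because the document does not reveal the intended value, and Step 5 shows that 5 s, 35 s centred and 35 s trailing give different answers.

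A second reply is that the filter may be meant for NIRS only. The step targets motion artifacts and ends by synchronising with the metabolic cart, which fits the 10-Hz stream, and VO2 already has the cart's breath averaging. That is plausible, but the text names both signals. HHb and TSI would be damaged in any case.

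Several stronger readings are tempting and are not supported:
- **All three phases mixed at every CWR point.** True only at about 125–175 s with a centred window, and never with a trailing one.
- **VO2peak biased, so the check of the 0.75 factor fails.** In Set A a peak of 16.0 would read about 11.1–12.1 (centred) or 13.6–14.1 (trailing) for true tau of 30–60 s, but only if taken from this series. VO2peak has its own 20-s definition, so this stays conditional.
- **A particular false tau.** The size depends on assumed amplitude, ramp slope and lag. Only the direction and the loss of information are robust.
- **Off-kinetics fail because the window outlasts recovery.** It does not; they are distorted because the window reaches back into the ramp.
- **The study fails on its main endpoint.** The primary outcome is feasibility of recruitment and completion.

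**Conclusion.** The stated rule is wrong as written and must be corrected. That a 350-s window exceeds the 300-s CWR and 180-s rest phases, and clashes with the plan's own features of 20 to 60 s, follows from the document alone. The sizes rest on assumed, noise-free profiles with true tau of 30 to 60 s: on-tau of roughly 300 to 2000 s centred and none identifiable trailing; off-tau of about 110 to 150 s centred and several hundred seconds or more trailing. The results at risk are the secondary physiological ones and, with a trailing window applied to VO2, the steady-state VO2 used for validation at CWR. Whether the analysis code actually uses 350 s cannot be told from the document.

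**What to change.** In Data Analysis:

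1. Replace the 350-second figure with the intended window and its unit (seconds or samples). It should be short relative to the expected time constants (seconds, not minutes) and centred rather than trailing. The document does not support naming one exact value or requiring unsmoothed VO2.
2. State whether it applies to NIRS, VO2 or both, and that it does not average across phase transitions.
3. State that the VO2peak and TSI windows are taken from data without this filter.
4. Check the setting in the LabVIEW code against the corrected text.

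The cost is one or two sentences and one parameter check. Testing procedures and data collection do not change.
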